## WITHDRAWAL FROM THE STUDY

Patient and practitioner participants will be free to withdraw consent at any time without providing a reason. Notice of withdrawal should be given to the Programme Manager at Southampton, via email to [[contact]](mailto:[contact]). When withdrawn, patient participants will continue to receive standard clinical care from their practitioner. Follow up data will continue to be collected (unless the participant has specifically stated that they do not want this to happen).

## CONFIDENTIALITY

The research team will preserve the confidentiality of participants taking part in the study. The investigators will ensure that participant's anonymity will be maintained and that their identities are protected from unauthorised parties. On trial documents and files participants will not be identified by their names, but by an identification code. The key to identification codes will be kept in a separate room to the trial data documents and files, in a locked cabinet within the University of Southampton Primary Care department at Aldermoor Health Centre.

## INDEMNITY

The University of Southampton's public and professional indemnity insurance policy provides an indemnity to UoS employees for their potential liability for harm to participants during the conduct of the research. This does not in any way affect an NHS' Trust's or GP Practice's responsibility for any clinical negligence on the part of its staff.

## DATA HANDLING

Participant data will be entered on laptop computers on site and retained at the University of Southampton in accordance with the General Data Protection Regulation (2018). The CI will be responsible for ensuring the accuracy, completeness, and timeliness of the data entered. Participant data will be pseudo-anonymised by assigning each participant a participant identifier code which will be used to identify the participant during the study and for any participant- specific clarification between the University and participating practices.

The Informed Consent Form will specify the participant data to be collected and how it will be managed or might be shared; including handling of all Patient Identifiable Data (PID) and sensitive PID adhering to relevant data protection law. Trained personnel with specific roles assigned will be granted access to the electronic patient data.

## MONITORING

Data stored at the Universities of Southampton, Liverpool, and Hull will be checked for missing or unusual values (range checks) and checked for consistency within participants over time. Any suspect data will be returned to the researcher or practice in the form of data queries.

The participants' anonymised data may also be reviewed by the Independent Data Monitoring Committee. Details will remain confidential and participants' names will not be recorded outside the University.

## RECORD RETENTION AND ARCHIVING

Study documents will be retained in a secure location during and after the trial has finished, in accordance with the sponsor University of Southampton's regulations. After study closure the CI will maintain all source documents and study related documents and retain them for a period of 10 years.

## PUBLICATION AND DATA SHARING POLICY

A REDUCE programme dissemination group has been established, whose purpose is to oversee the planned outputs from the REDUCE programme, and agree on data sharing arrangements. This group comprise the CI [name] (TK) in Southampton and one PI from each centre (York ([name]), Liverpool ([name]), and London ([name]). All correspondence will be handled in the first instance by the Programme Manager [name] on behalf of TK. A copy of the publication and data sharing policy is available on request.

# **1 Introduction**

## **1.1 Purpose of SAP**

This statistical analysis plan (SAP) describes in detail the methods that will be used to analyse the data collected as part of the REDUCE trial. This will form the basis of the final trial publication. The final analysis will follow the SAP to ensure that the analyses are conducted in a scientifically valid manner and to avoid post hoc decisions which may affect the interpretation of the statistical analysis. Any deviations from the SAP will be detailed in the final report.

## **1.2 Trial background and rationale (from ISRCTN registration)**

Work Stream 5 (WS5) of the REDUCE programme aims to determine the effectiveness of online (Internet) interventions which support practitioners and guide patients on coming off antidepressants, together with psychological practitioner telephone calls to support the patients.

We will assess the effectiveness of the interventions in terms of reductions in antidepressant use in the absence of worsening of depression, and assess patients' and practitioners' use of the interventions (automatically recorded by the Southampton 'LifeGuide' software used for the Internet guidance).

## **1.3 Objectives (from published protocol)**

1. To determine the effectiveness of the intervention through a randomised controlled trial
2. To estimate cost-effectiveness from a health and personal social service perspective, with a sensitivity analysis from a societal perspective.

The analysis required to evaluate the first of these objectives will be set out in this Statistical Analysis Plan. The analysis required to evaluate the second objective will be set out in a separate Health Economics Analysis Plan.

## **1.4 Definition of endpoints**

### **1.4.1 Definition of primary endpoint**

The PHQ-9 scores for depressive symptoms at 6 months.

### **1.4.2 Definition of secondary endpoints**

- The PHQ-9 score over the full 12 month period as a repeated measure analysis
- Discontinuation of antidepressants at 6 months
- Antidepressant withdrawal symptoms measured on the Discontinuation Emergent Signs and Symptoms scale (DESS) over the trial period
- Anxiety on the GAD-7 measure of generalised anxiety disorder over the trial period
- Wellbeing scores over the trial period on the Warwick-Edinburgh Mental Wellbeing Scale (WEMWBS)
- Modified version of the Medical Informant Satisfaction Scale (MISS) over the trial period to measure patient satisfaction over the follow-up period.
- Patient enablement measured by the Patient Enablement Instrument (PEI) over the trial period

## **1.5 Analysis principles**

All analyses will be reported in line with the CONSORT 2010 extension to cluster randomised trials and non inferiority trials and Southampton Clinical Trials Unit (SCTU) standard operating procedure (SOP) on planning, implementing and reporting statistical analyses (CTU/SOP/5058).

## **2 Design considerations**

### **2.1 Description of trial design**

This is a pragmatic multicentre cluster randomised non-inferiority trial.

### **2.2 Trial power and sample size**

To have 90% power, with a one-sided alpha of 2.5%, to establish non-inferiority in terms of depressive symptoms within two points (estimated to be the minimal clinically important difference) on the PHQ-9 at 6 months (standard deviation 5.4), we need 155 patients followed up in each arm. Assuming a variable cluster size of between 1 and 7 per practice (mean 3) and an intra-cluster correlation coefficient of 0.012 (from the Health Technology Assessment THREAD trial of treating mild-to-moderate depression in primary care), gives a 1.033 cluster design effect (based on a coefficient of variation of  $1.5/3 = 0.5$ , using the formula of Eldridge). Anticipating 20% do not comply with the intervention and/or are lost to follow-up, we need to randomise  $(155 \times 2 \times 1.036) / 0.8 = 402$  patients (201 per arm) from 134 practices (67 per arm).

Following discussion with the study steering committees and the funder, the sample size was amended to 360 participants. This allows for a correlation between baseline and follow-up scores with a deflation factor of  $1 - \rho^2$ . At the time of review we observed a correlation of 0.47 but were unsure whether this would persist to the end of follow up for all participants. If we assume the more conservative estimate of correlation of 0.26 (the bottom end of the CI), the target sample size to achieve 90% power would 375. We assume the final figure will be somewhere in between 0.26 and 0.47, and that a sample of around 360 will therefore provide us with the necessary 90% power to test reliably for non-inferiority of the intervention in terms of depressive symptoms.

### **2.3 Randomisation details**

Randomisation of practices is by computerised sequence generation, and minimisation with a random element using three factors to avoid imbalance between the two arms: practice size (large/small), location (urban/rural) and social deprivation (dichotomised around the median Index of Multiple Deprivation score). The allocation ratio is 1:1 but there is a random element to the minimisation algorithm and so we might not expect perfect balance to the randomisation.

### **2.4 Timing of planned analyses**

#### **2.4.1 Interim analyses and early stopping**

No interim analysis is planned and no pre-specified stopping rules have been established.

#### **2.4.2 Final analysis**

End of study is defined as when the last patient has had their last data collected, cleaned and verified.

### **3 Statistical considerations**

#### **3.1 Definition of analysis populations**

##### **3.1.1 Intention-to-treat analysis population**

This population includes all randomised practices and all patients recruited within them regardless of treatment compliance. This includes the participants recruited during WP4 and treated as an internal pilot. All summaries and analysis will be on the modified ITT population unless otherwise specified, i.e. the population as randomised but without missing data imputed. The ITT analysis will be the primary analysis.

##### **3.1.2 Per-protocol analysis population**

In a non-inferiority trial where some patients do not comply with treatment as randomised, the difference between the arms can appear reduced and the groups look more similar, leading to the incorrect conclusion of non-inferiority. A per-protocol analysis would analyse individuals based on their compliance with treatment as randomised, excluding non-compliant participants, which may give a more conservative estimate of effect for non-inferiority. However, the exclusion of some participants after randomisation can potentially lead to bias. Therefore, we will present both intention-to-treat and per-protocol analyses. The ITT analysis will be the primary and the per-protocol analyses will be treated as secondary.

##### **3.1.3 CACE analysis population**

We will also undertake a complier-average causal effect analysis, which is another approach for dealing with non-compliance that compares compliant participants in the intervention group with those in the control group whose characteristics are similar enough to the intervention group compliers to suggest they too would have complied with the intervention given the opportunity to do so. Compliance for these analyses in the intervention arm will be defined as completing the first session of the LifeGuide programme within 6 months of recruitment (anticipating >90%). The first session will have information about antidepressant treatment, the rationale for attempting withdrawal, and how withdrawal should be attempted under supervision. We would expect patients to benefit from that session even if they do not log on again.

#### **3.2 Analysis software**

SAS v9.4 or higher, or Stata v15.1 or higher will be used for all analyses.

#### **3.3 Methods for handling data**

##### **3.3.1 Withdrawal from trial**

All data up until the point of patient withdrawal from the trial will be used in analyses unless the patient withdrew consent and does not wish for the data already collected prior to withdrawal to be used for the trial.

If a practice withdraws from the trial, no further patients will be recruited. All data on patients collected until that point will be used and any patients recruited will continue to be followed up in accordance with the trial schedule.

### **3.3.2 Missing data**

The primary analysis will be of complete cases.

If more than 2 items in the PHQ-9 and the GAD7 have missing values, the total score will be missing. If one or two items are missing, the score will be imputed with the mean of the non-missing scores before summing.

We will examine the structure and pattern of missing data and, if appropriate, will present a sensitivity analysis based on data imputed using a chained equations multiple imputation model. The imputation model would include the outcome measure, baseline value of the outcome, randomisation group, clustering by practice and all covariates included in the analysis model (see below)

### **3.3.3 Outliers**

No methods will be used to handle outliers in the data, except in the regression models. If outliers are found then firstly the source data will be checked. If the source data is correct, then a sensitivity analysis will be performed excluding them from the analysis.

### **3.3.4 Assumption checking and alternative methods**

Assumptions for linear regression models (linearity, normality, homoscedasticity) will be checked using scatter plots of standardized residuals against fitted values, and qq plots. If linear models are not appropriate a log-linear transformation will be used.

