### Baseline telephone screening

Patients will be assessed by telephone and excluded if they have any of the exclusion criteria listed above. Exclusion criteria include significant depressive symptoms despite antidepressant treatment, defined as a score of 12 or more on the Patient Health Questionnaire (PHQ-9) (Kroenke 2001) completed over the telephone. The PHQ-9 is a self-complete questionnaire taking approximately three minutes. It measures nine core symptoms of depression based on Diagnostic and Statistical Manual (DSM-IV) criteria and has high sensitivity and specificity in UK primary care (Gilbody 2007).

Patients will also be excluded if they have significant anxiety at baseline, i.e. a score of 10 or more on the 7-item Generalised Anxiety Disorder scale (GAD-7), also completed over the telephone. The GAD-7 is a brief screening instrument for anxiety also validated in primary care (Spitzer 2006). Though originally developed to detect GAD, it also has good sensitivity and specificity for panic, social anxiety, and post-traumatic stress disorders (Kroenke 2007).

If patients score above 0 (i.e. 1, 2 or 3) on the 9th question of the PHQ-9, about suicide/self-harm, they will be excluded from participating, and this information will be relayed to their GP immediately for them to discuss this, preferably with their permission. The information may be relayed without their permission if necessary, after discussion between the researcher, the principal investigator, and the patient.

If patients are excluded at baseline screening due to either a total PHQ-9 depression score of 12 or more, or a score of 1 or more on the self-harm question 9 of the PHQ-9, or a total GAD-7 anxiety score of 10 or more, and they wish to be reconsidered for inclusion at a later date, they may consent to being recontacted in three months to be re-screened. At re-screening, they may be included in the study if those exclusion criteria no longer apply.

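### SAP 3.3.4 does not exempt the primary PHQ-9 analysis from its log fallback, so a failed model check would replace the 2-point non-inferiority test with a ratio that has no stated margin

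*Combined protocol and SAP*

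**What the plan says.** - **Margin.** SAP 2.2 powers the trial "to establish non-inferiority in terms of depressive symptoms within two points" on the PHQ-9 at 6 months, with an SD of 5.4. The protocol's sample size section gives the same margin. Neither document states a margin on another scale.
- **Scale.** SAP 3.4 gives a PHQ-9 range of 0 to 27, with higher scores worse.
- **Primary model.** SAP 4.4 specifies a linear mixed model of 6-month PHQ-9, judged from a limit of the 95% confidence interval. The same analysis is repeated for the per-protocol and CACE populations.
- **Fallback.** SAP 3.3.4 checks linearity, normality and homoscedasticity from residual and qq plots, and then says: "If linear models are not appropriate a log-linear transformation will be used". It sets no objective trigger.
- **Outliers.** SAP 3.3.3 has source data checked first and then says: "If the source data is correct, then a sensitivity analysis will be performed excluding them from the analysis". It does not define an outlier.
- **Entry.** Under the protocol's baseline telephone screening, a PHQ-9 of 12 or more excludes the patient.

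**The concern.** A population that enters below 12 on a scale with a floor at 0 is likely to have many low 6-month scores and a right tail from relapse. The protocol's list of expected adverse events anticipates relapse in 10-20% of patients over one year. Residual plots may then look skewed, and the SAP's instruction at that point is to move to a log scale.

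Three things would then have to be chosen after the data are seen: how to handle zeros, how to turn 2 points into a ratio, and how to report the result in points. SAP 1.1 says that the plan exists to prevent such choices. At stake is whether the primary hypothesis is tested as planned and with its stated error rate.

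**Working it through.** **1. The plan's own figures are on the raw scale.** With one-sided alpha 2.5%, 90% power, margin 2 and SD 5.4:

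n = 2 × 5.4² × (1.960 + 1.282)² / 2² = 153.2, so 154 per arm against 155 stated.

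Design effect = 1 + ((0.5² + 1) × 3 − 1) × 0.012 = 1.033, as stated. The total is 155 × 2 × 1.036 / 0.8 = 401.5 (400.3 with 1.033), against 402 stated. The deflation factors give 402 × (1 − 0.26²) = 375 and 402 × (1 − 0.47²) = 313, as stated. The sample size reproduces, and all of it depends on a difference in points.

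**2. Two points have no single log equivalent.** The documents give no expected control mean at 6 months, so a range is assumed:

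| Control mean | Ratio (mean + 2)/mean | Log margin | Log margin on x + 1 |
|---|---|---|---|
| 3 | 1.67 | 0.51 | 0.41 |
| 4.5 | 1.44 | 0.37 | 0.31 |
| 6 | 1.33 | 0.29 | 0.25 |
| 10 | 1.20 | 0.18 | 0.17 |

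**3. The log changes what a point is worth.** On log(x+1), a rise from 1 to 3 counts log(4/2) = 0.69. A rise from 15 to 17 counts log(18/16) = 0.12.

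**4. Error rates at the margin.** Assumptions:
- 360 × 0.8 / 2 = 144 analysed per arm
- negative binomial scores capped at 27, with mean/SD of 3/3.5, 4.5/4.5 and 6/5.4
- no clustering or covariates
- 4,000 trials per setting
- difference taken as intervention minus control, so the upper 95% limit is compared with the margin
- a true difference of about 2 points, so that declaring non-inferiority is an error (nominal rate 2.5%)

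| Analysis | Pattern of harm | Mean 3 | Mean 4.5 | Mean 6 |
|---|---|---|---|---|
| Raw | 20% of intervention patients gain about 10 points | 2.9% | 2.8% | 2.3% |
| Log(x+1), margin converted at control mean | same | 14.6% | 6.9% | 4.6% |
| Log(x+1), margin converted at control mean | everyone gains 2 points | 0.0% | 0.0% | 0.0% |

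Zeros made up 9-26% of control scores. The 0.0% row arises because log((x+3)/(x+1)) is a convex function of x. Averaged over skewed scores it exceeds its value at the mean, so a uniform 2-point shift lies beyond the converted margin.

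**5. The reference mean matters as much.** A second set of assumptions used control means of 4 to 6, with an extra 13-15% of intervention patients scoring 15-24. The raw test gave 2.5-3.0%. Log(x+1) gave 7-23% with the margin converted at the arithmetic control mean, and 23-54% at the geometric mean. The SAP specifies neither.

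**The case against.** SAP 3.3.4 is a general clause and applies only if checks fail. SAP 4.4, the specific section, names a linear mixed model and no transformation, and SAP 1.1 requires deviations to be reported. The checks are on residuals from a model adjusted for baseline PHQ-9, anxiety and other covariates, so skewed raw scores need not produce a failure. All of this is fair, and it makes the problem conditional. It does not remove it, because nothing in 3.3.4 or 4.4 says that the primary outcome is exempt.

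A reader might also infer more than the documents support:

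- **That zeros make the analysis impossible.** They defeat only a plain log of the score. Log(x+1) is available, and if log-linear means a log-link model, zeros are accepted and a mean difference can be recovered. The SAP does not say which is meant.
- **That a margin cannot exist on the log scale.** It can be converted, given a reference mean and, for a transformed score, a constant. The SAP supplies neither.
- **That the log always favours non-inferiority.** It does so when harm falls on a relapsing minority. Under a uniform shift it goes strongly the other way.
- **That verified high scores are dropped from the primary test.** SAP 3.3.3 excludes them only in a sensitivity analysis, so the primary result keeps them.

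**Conclusion.** The point holds as a conditional gap in the primary analysis. If the fallback is triggered, the 2-point test is replaced by a ratio for which the SAP gives no margin, constant or back-transformation. The test also loses its calibration, in a direction set by how harm is distributed: about 4-15% false non-inferiority for relapse-type harm and about 0% for a uniform shift, against about 2.5-3% on the raw scale. At the only setting that uses the plan's own SD (5.4, with an assumed mean of 6), the relapse-type figure is at the low end, at 4.6%.

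These rates rest on assumed control means, score distributions, relapse patterns and the log(x+1) form. The gap in the wording does not depend on them. In the relapse-type simulations the raw analysis kept close to its nominal rate despite the skew, so the transformation is not needed to protect the test. The stated sample size is unaffected.

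**What to change.** In SAP 3.3.4, state that the primary PHQ-9 non-inferiority test, in the ITT, per-protocol and CACE analyses, stays on the raw 0-27 scale against the 2-point margin. Add that if residuals are skewed or heteroscedastic, the 95% confidence interval for the raw mean difference will come from a practice-level bootstrap or from practice-clustered robust standard errors. Name one of the two as the default. Any log-scale analysis should be labelled supplementary, with its model form and constant stated.

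In SAP 3.3.3, at most one sentence is needed: an analysis that excludes source-verified values cannot be used to support a non-inferiority conclusion.

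The cost is a few sentences before unblinding and a standard option in SAS or Stata. No endpoint, population, margin or sample size changes.

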## **3.4 Definition of key derived variables**

The PHQ-9 is a self-complete questionnaire taking approximately 3 min to complete. Each item is scored 0-3 with a total possible score ranging from 0-27. Higher scores indicate more severe symptoms.

The Generalised Anxiety Disorder Assessment 7-item version is a self-report measure of anxiety symptoms. Each item is scored from 0-3 with a total possible score ranging from 0-21. Higher scores indicate more severe symptoms.

Discontinuation of antidepressants is deemed to have occurred once the patient has stopped taking them for 2 months. This is a binary outcome (did not discontinue/did discontinue).

The Warwick–Edinburgh Mental Wellbeing Scale (WEMWBS) measures both subjective experiences of happiness and life satisfaction (the ‘hedonic perspective’), and positive psychological functioning, good relationships with others and self-realisation (the ‘eudaimonic perspective’). Each item is answered on a 1 to 5 Likert scale and summed to give a total score ranging from 14 to 70. Higher scores indicate greater wellbeing.

Antidepressant withdrawal symptoms are measured using the Discontinuation Emergent Signs and Symptoms scale, a brief self-report measure on which participants can indicate the presence of, and

changes in, 43 possible antidepressant withdrawal symptoms. The total number of symptoms is summed.

The 29-item 'Medical Interview Satisfaction Scale' (MISS-29) was developed in the USA to assess patient satisfaction with individual doctor-patient consultations and has been shown to be valid and reliable in UK primary care.

The modified Patient Enablement Instrument asks 6 questions about the patients' ability to understand their problems and cope with illness. These are rated on a 7 point Likert scale (0=strongly agree to 7=strongly disagree). A mean overall score can be calculated, with lower scores equating to better enablement.

